#### Data collection

Individual conversational interviews will be carried out with PCHP. They will be asked about their individual experience and the significance of receiving displays of gratitude from P/R.

#### Guideline development and interview process

The interview guide will be designed taking the survey results and literature review into account. It is foreseen that HP will be encouraged to tell of their specific experiences of displays of gratitude from P/R they have cared for and to talk of what these displays actually meant to them, the significance for them and use they have made of the same.

The interviews will be conducted face-to-face or by video link, after earlier agreeing on the day and time with the interviewee. The interview will begin with a general question as an introduction and depending on the participants’ narrative, there will be a combination of scripted open questions, together with other dialogue questions, with the aim of widening the scope of the answers offered by the participants, allowing them to clarify their statements or to request specific examples of situations they have lived.

If needed for deepening or clarification, a further interview might be carried out with the HP to go into greater depth and to understand their experience [84].

Interviews will be audio recorded and then transcribed for analysis.

#### Pilot interviews

The lead researcher will conduct all the interviews ([name]). Since personal interview skill development is essential, a number of pilot interviews will be conducted, for which feedback from an expert in interviews ([name]) will be provided on how to encourage respondents to talk and to elicit experiential narrative material, stories or anecdotes, that may serve as a resource to develop a richer and deeper understanding of the gratitude phenomenon and how to use different probing strategies –if needed [85]. The purpose of the pilot is mainly to improve interviewer’s skills, who has already previous experience on conducting qualitative research so it is estimated that 2–3 interviews may be enough to adjust the interviewing skills to a phenomenological approach. The data of the pilot interviews will not be included in the data analysis.

#### Data analysis

Transcriptions will be literal, word for word, in order to maintain the richness of the data and encourage rigour. They will undergo phenomenological centred qualitative analysis [85], since this is suitable for describing factors common to experiences in HP, given that this method studies how people construct meaning from lived experiences [86]. To do this, specific themes from transcriptions will be taken separately and reflected upon on two levels: macro-thematically and micro-thematically to deep on the essence of the lived experience of receiving gratitude displays from P/R. Using macro-thematic reflection, after reading the text, one or more judgmental statements will be made regarding the fundamental meaning of the text (from the interview) or the importance of the same overall. Using this approach, we try to answer the questions, “What does this text say about the meaning of the phenomenon which we are studying?” “Which judgmental statement or statements might embody the fundamental meaning or the main idea behind the text overall?” [85, 87–89].

Then a micro-thematic reflection will be undertaken, on two levels [88]. To begin with, using the selective approach, the text will be read a number of times, considering which statement or statements seem to be especially important or revealing, on the phenomenon or experience being described. Then, those which seem to reveal a thematic aspect of the phenomenon will be highlighted. Secondly, using a detailed, or line-by-line approach, each statement or group of statements will be reviewed individually, whilst reflecting on what that statement or group of statements reveal about the experience of demonstrations of gratitude.

As the selective approach progresses, so will the process of beginning to edit those fragments which reveal any thematic aspect on the experience lived from gratitude, transcribing this content in literal fragments which may be used as examples of lived anecdotes.

The analytical process will be undertaken by one of the researchers ([name]) under the constant supervision of an expert in qualitative research ([name]). Throughout the analysis process, meetings will be held to reflect on the interpretative process and the results emerging with another PC expert ([name]).

### Ethical aspects

The Research Ethics Committee of the Universidad de Navarra approved the study with the number 2016.071.

In the study, an information sheet will inform all participants about the different phases of the project in which they are participating, explaining the context, aims, implications of taking part and the ethical aspects.

In both the quantitative and the qualitative study, participants will receive information on the implications of their taking part and the possibility of dropping out whenever they wish.

In the case of the survey it is assumed that by accepting to complete and send it, participants are giving their consent to take part of it. As for the interviews, an additional signed consent form will be required.

Norms regarding confidentiality and rigour in scientific research will be observed in handling personal details. Data from the questionnaires will be anonymous and the details for HP who agree to be contacted for the interview phase will be kept on a separate database from that for the questionnaire and will be confidential.

Interviewees will be identified by a code and only the research team will have access to the same. In case results are published, only individual fragments will be cited, in such a way that identification of the participants will not be possible.

As well as ensuring that all the data is stored securely, the study will be carried out in compliance of current legislation on data protection (LO 15/99 on *Protección de Datos de Carácter Personal y su Reglamento de Desarrollo*).

## Discussion

This study will tackle the gap identified in the literature. The literature reviewed suggests that displays of gratitude received from P/R seem to have a positive effect on HP [4]. This literature consists of individual reflections of HP who tell their experience and mention that receiving gratitude from P/R leads to feelings such as well-being [22], recognition [25, 27], satisfaction [22–25], motivation [23] and even personal and professional repercussions [25, 27, 28, 90]. The characteristics and impact of receiving gratitude have not been fully examined and this has never been done systematically in PC. HP in this area are especially exposed to situations of suffering and this makes research into the potentially beneficial effects of gratitude received from P/R especially interesting to offer a resource that can help us to carry on in our daily duty; even if we do not do our work expecting to receive gratitude.

The objective of this study is to understand the experience of gratitude received when caring and its significance for PCHP, by means of a mixed method research.

The use of a mixed method design provides a broad approach to explore the topic, which is adequate to explore a complex little known phenomenon. The first part of the study will allow the systematic study of a large sample of HP working on PC services and their experiences of gratitude. As any self-reporting study it has limitations regarding recall bias. Considering the literature about the possible effect of gratitude displays and the value that HP give to them (ie: they keep letters and gifts), this may be minor to other situations. The questionnaire includes open questions on which they describe experiences obtaining details that otherwise may be overlooked. It has been carefully planned to reach all the PC services, containing all the possible types of PC resources, as mentioned earlier, promoting representativeness. The member of the team that publicly appears like the service contact is the one that receives the questionnaire. This person is usually the head of the service so it is assumed that will have an overall view of the phenomenon. This view may differ from other members but allows to provide a general national view of the gratitude displays that PCHP receive as all the PC services are included. To our knowledge, this would be the first study to this regard with such a large coverage.

A careful plan has been developed to improve the response rate but in spite of this there will be non-respondents. It is not planned to gather information from these because it has been prioritized the objective of deepening on the gratitude experiences, developing the qualitative part of the study. In it, the results obtained in the survey will be taken into account but prioritizing in deepening in the lived experiences of the HP. It is planned to reduce the limitations of having only participants of the survey for the interviews, considering the inclusion of other participants interested in the subject. In studies with a phenomenological approach, the key to the quality of the study is not based as much on the number of participants as on the richness and depth of the data obtained. For this reason, a pilot phase has been designed to refine the skills of the interviewer and carry out a quality study advised by an expert. Besides, different measures have been planned to assure enough interviewees to reach saturation.

The quantitative part will provide an initial examination of the phenomenon, by means of a nationwide survey, to obtain general information on the subject and to evaluate the true situation of displays of gratitude in PC and their self-reported repercussion. The qualitative part will add deeper insight on the significance and role that displays of gratitude received from P/R have for PCHP.

This study has the strength to demonstrate with a national coverage, the wider view about the characteristics of the gratitude displays received in PC services from P/R, and the meaning, impact and significance that this gratitude has for the PCHP.

This study contribution could be important within the context of the growing preoccupation on how to care for HP, how to ensure retention and keep them on as part of the teams at institutions, how to prevent burnout, fatigue issues and loss of motivation, which might give rise not only to impersonal care but also to increased absenteeism at work. If the results confirm the positive effects mentioned anecdotally in literature, this will give rise to an interesting field of study on expressions of gratitude as a source of resources to tackle burnout or to enhance resilience.

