#### Population and sample size calculation

The target group is PCHP specifically dedicated to PC. There are some teams that attend PC patients and another kind of no PC patients, but these were not the focus of the study as their challenges and situation are different [59].

In Spain, PC development has been gradual covering all levels of attention as hospitals, residential and community [60]. In general, it is estimated that there is 1 resource of PC for 102.026 inhabitants, although it varies depending on regions. The PC coverage is through different types of resources: PC units, PC support teams in the community, PC support team in the hospital, PC mixed supports teams (community and hospital). There are also paediatric PC units and support teams. PC services include different HP, sometimes have the basic structure of doctors and nurses and others a more complete one including social worker, psychologist, physiotherapists and others [59].

In the absence of a census of PCHP the PC service directory is considered the best option for the study. The directory is developed by the Spanish Society for Palliative Care [60]. Its latest version is from 2015 and lists all the services of PC known in Spain and has an email of contact for each of these services [60]. This contact usually is the head, the lead or the manager of the team as well as the one who kind of represents the whole team. Expressions of gratitude often are addressed to them even if there are for the whole team, so is a rich informant about gratitude. It is decided to include all the services in the list to enhance representativity [61]. The sample will be made up of one member from each service.

In case a particular service does not have an e-mail address, contact will be made by telephone to obtain the email and thus complete the list to the greatest possible degree [62].

The sample will include representatives of all the PC services in Spain (*n* = 284), and as such, the total sample will be used. This is a scientific survey method to allow the drawing of robust conclusions for the whole population [63], especially on an area where there is no available data such as proportion expected or relevant minimum effect; previously published to calculate sample size [61, 62, 64].

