The experience of gratitude is an area of limited knowledge, with no published information about its frequency, impact, and effect. So as it is difficult to estimate the sample size needed, a total sample approach was chosen. Having a total sample size of 284 will allow a robust exploration of the phenomenon of study.

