#### Survey process

The questionnaire will be sent to the e-mail contact at each PC service, using the survey platform Survey Monkey®.

The response rate to surveys varies in relation to the type of questionnaire, the aims and format as regards administration [70]. In self-administered web-based questionnaires, the estimated response rate is between 24% [71] and 42% [72].

Since the representativeness of the results, depends not only on the sample but also on response rates, available evidence has been used to design a plan to stimulate a higher rate of response, including:A personal e-mail or cover letter indicating that a questionnaire will be sent shortly [65, 68, 73–75] including the topic, goals and the study information sheet.The identification of the study’s authors will be stated in the e-mail together with the promise to inform them of the principal results [76].Identification of the institution sponsoring the study, including its logo [74, 76].A personal invitation to take part in the study, including the link to the questionnaire [68].The questionnaire is sent at the beginning of the week, avoiding vacation periods [75].Follow up with weekly reminders [62, 68, 73] for 3 weeks, only for those people who have not completed the questionnaire [73, 75]. This will be done automatically set up to do it at the survey monkey platform, without the need to screen who has answered or not.A thank you e-mail for those who have completed the questionnaire [62, 68, 73–75].Offers of incentives [62, 65, 68, 74]. In this instance, the incentive offered to one of the participants is enrolment on a research course provided by the Instituto Cultura y Sociedad of the Universidad de Navarra. As well as literature indicating that incentives help increase response rates, it also rewards the time dedicated to completing the questionnaire. This incentive will be mentioned in the informative e-mail and the raffle will be held once everyone has completed the survey. The winner will be contacted by one of the members of the research team.

As such, the following guidelines for monitoring and administration have been drawn up (Table 1).

**Table 1 Tab1:** Protocol for survey follow up

Week 1	An advisory e-mail is sent to the whole sample with a personal invitation, advising them that they will soon receive a questionnaire, together with an information sheet on the study.
Week 2	A personal e-mail with a link to the questionnaire is sent to the whole sample.

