Week 3	Follow Up 1: The first reminder with a link to the questionnaire is sent to all those who have not replied or have only partially replied.
Week 4	Follow Up 2: A second reminder with a link to the questionnaire is sent to all those who have not replied or have only partially replied.
Week 5	Follow Up 3: The third reminder with a link to the questionnaire is sent to all those who have not replied or have only partially replied.
Week 6	A personal e-mail thanking them for their participation is sent to all those who have completed the questionnaire fully.

Should the response rate be less than 55–60%, the contact details of the non-respondent services will be checked with a phone call to the service to update the contact details. Then the questionnaire will be sent again using updated data for these services and following the protocol mentioned above except for the invitation mail and the third reminder.

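### The national claims rest on every service being invited, while the plan accepts non-response and includes no check of who replied

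*Protocol article*

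**What the plan says.** The survey goes to one contact at each service in the national directory. Under Population and sample size calculation the reason is given as "It is decided to include all the services in the list to enhance representativity", and the total-sample approach is said to support firm conclusions about the whole population. The same section adds: "Having a total sample size of 284 will allow a robust exploration of the phenomenon of study".

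Survey process takes a more careful line: "Since the representativeness of the results, depends not only on the sample but also on response rates". It cites response rates of 24% to 42% for self-administered web questionnaires and says that "available evidence has been used to design a plan to stimulate a higher rate of response". The measures are advance notice, three weekly reminders and a prize draw. There is also a fallback: "Should the response rate be less than 55–60%, the contact details of the non-respondent services will be checked with a phone call". After that call the questionnaire is sent again.

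The Discussion accepts that non-respondents will remain and says: "It is not planned to gather information from these because it has been prioritized the objective of deepening on the gratitude experiences". It nevertheless presents the survey as giving a picture for the whole country because every service is covered, and concludes: "This study has the strength to demonstrate with a national coverage". For the survey, Data analysis describes summary statistics and possible relationships between variables.

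**The concern.** The article holds two positions that do not fit together. Survey process says that representativeness depends on who answers. The sample-size section and the Discussion draw the national conclusion from who was invited. A complete invitation list removes the error from choosing a sample, but it does nothing about selection by reply.

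That selection may be related to the outcomes. According to Survey process, the advance e-mail states the topic and goals. The questionnaire asks how often gratitude is shown, what it means to the respondent and how far it helps. Contacts who value gratitude may be readier to answer, and would probably give higher ratings. The remedy offered in the Discussion, recruiting further interviewees interested in the subject, serves the qualitative phase and does not bear on this.

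The stated goal of the first phase is the current situation in Spain, and its results shape the interview guide. If the plan is followed as written, the proportions would be reported as national with nothing to show whether the respondents resemble the list.

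**Working it through.** The figure of 284 is a count of listed services, with no sample-size formula behind it, so there is nothing to reproduce.

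**Inputs from the protocol article**
- Services invited: N = 284 (Population and sample size calculation).
- Response cited for web surveys in general: 24% to 42% (Survey process).
- Response below which services are re-contacted: 55–60% (Survey process, after Table 1).

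**Assumed inputs**
- Difference d between respondents and non-respondents on a reported proportion: 10 or 20 points. The article gives no figure.
- For the worst-case range: 80% of respondents report an item.

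**Formulas**, with response rate r and n = 284 × r rounded to a whole number
- Non-respondents = 284 − n.
- Bias of the respondent proportion as a national figure = (1 − r) × d.
- Sampling margin (95%, p = 0.5) = 1.96 × √(0.25/n) × √((284 − n)/283). This treats the replies as a random subset and is given only for comparison.
- Worst-case range: from 0.8 × n/284 (no non-respondent reports the item) to (0.8 × n + 284 − n)/284 (all of them do).

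| Response | Replies | Non-respondents | Bias, d = 10 | Bias, d = 20 | Sampling margin | Worst-case range |
|---|---|---|---|---|---|---|
| 24% | 68 | 216 (76%) | 7.6 | 15.2 | 10.4 | 19–95% |
| 42% | 119 | 165 (58%) | 5.8 | 11.6 | 6.9 | 34–92% |
| 55% | 156 | 128 (45%) | 4.5 | 9.0 | 5.3 | 44–89% |
| 60% | 170 | 114 (40%) | 4.0 | 8.0 | 4.8 | 48–88% |

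Bias and margin are in percentage points.

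**Where bias overtakes sampling error.** Setting (1 − r) × d equal to the margin gives d = 10.4/0.76 = 13.7 points at 24% response, 6.9/0.58 = 11.9 at 42%, 5.3/0.45 = 11.8 at 55% and 4.8/0.40 = 12.0 at 60%. Below a difference of about 12 to 14 points, sampling error is the larger of the two. Above it, non-response bias is.

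**The case against.** The best defence is that the survey is the smaller part of the study. The qualitative phase has stated priority, the survey goal is exploratory, and the authors disclose the choice and give a reason. The analysis section is condensed, so the absence of a table comparing respondents with the list would not by itself be a finding. All of this lowers the weight of the point. It does not remove it, because the national inference is stated outright and conflicts with what Survey process says about response.

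Several stronger readings are tempting, and the article does not support them:
- *That 58–76% of services are expected not to answer.* This is the complement of a general literature range that the plan sets out to beat. The re-contact trigger makes 40% to 76% the fairer span, though a trigger does not guarantee that the rate is reached.
- *That any look at non-respondents is ruled out.* The Discussion declines only to collect information from them. It does not exclude comparing respondents with the list.
- *That the directory already describes the non-respondents.* The article says only that it lists known services with a contact e-mail for each. Types of resource and regional variation are described for Spain in general, not as fields of the directory. The characterising questions are in an additional file that is not shown.
- *That the results are biased upward.* This is plausible but not shown, and its size depends on an assumed difference.
- *That weighting would cure it.* Weighting by type and region would leave selection on interest within those groups untouched. With about 68 replies the cells could be sparse.

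**Conclusion.** The point stands as a mismatch between the claim and the design. The article makes representativeness conditional on response, accepts non-response, and then states national conclusions because every service was invited. Between about 114 and 216 of the 284 services could be silent. The resulting error in a national proportion would be 4 to 8 points for an assumed 10-point difference and 8 to 15 points for an assumed 20-point difference. Even 60% response leaves a worst-case range of 48% to 88% when 80% of respondents report an item.

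These sizes illustrate and do not forecast. The response span comes from the article; the differences and the 80% are assumptions. The change should be made, but the matter is moderate, since the qualitative phase has priority and the decision is disclosed.

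**What to change.** 1. **Compare respondents with the list.** State that responding services will be compared with all 284 on whatever variables the directory and the characterising questions share, such as type of resource or region if both record them. Do this in aggregate, respondent totals against list totals, so that the anonymity promised under Ethical aspects is kept.
2. **Compare early with late replies.** Set the main results from early replies beside those received after the later reminders or in the second round, grouped by reply date. This assumes that the platform stores the date, which the article does not say. Read the comparison as indirect evidence on the direction of any bias.
3. **Reword the national claims.** In Population and sample size calculation and in the Discussion, make the claim rest on the achieved response and on checks 1 and 2, not on all services having been invited. Report the response rate beside it.

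Post-stratification can be an optional sensitivity analysis if the list holds the variables and the cells are large enough. It should be described as not correcting for interest in the topic.

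The cost is a few hours of analysis and a less favourable statement of national coverage. No new contact with non-respondents is needed, so the reason given in the Discussion for not pursuing them is respected. If the directory and the questionnaire share no variable, check 1 falls away, and the wording under 3 should say so.
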